## Abstract

**Background:**

Sterile water injections have been used as an effective intervention for the management of back pain during labour. The objective of the current research is to determine if sterile water injections, as an intervention for back pain in labour, will reduce the intrapartum caesarean section rate.

**Methods/design:**

***Design:*** A double blind randomised placebo controlled trial

***Setting:*** Maternity hospitals in Australia

***Participants*****:** 1866 women in labour, ≥18 years of age who have a singleton pregnancy with a fetus in a cephalic presentation at term (between 37 + 0 and 41 + 6 weeks gestation), who assess their back pain as equal to or greater than seven on a visual analogue scale when requesting analgesia and able to provide informed consent.

***Intervention:*** Participants will be randomised to receive either 0.1 to 0.3 millilitres of sterile water or a normal saline placebo via four intradermal injections into four anatomical points surrounding the Michaelis’ rhomboid over the sacral area. Two injections will be administered over the posterior superior iliac spine (PSIS) and the remaining two at two centimetres posterior, and one centimetre medial to the PSIS respectively.

***Main outcome measure:***Proportion of women who have a caesarean section in labour.

***Randomisation:*** Permuted blocks stratified by research site.

***Blinding (masking):***Double-blind trial in which participants, clinicians and research staff blinded to group assignment.

***Funding:***Funded by the National Health and Medical Research Council

***Trial registration:***Australian New Zealand Clinical Trials Registry (No ACTRN12611000221954).

**Discussion:**

Sterile water injections, which may have a positive effect on reducing the CS rate, have been shown to be a safe and simple analgesic suitable for most maternity settings. A procedure that could reduce intervention rates without adversely affecting safety for mother and baby would benefit Australian families and taxpayers and would reduce requirements for maternal operating theatre time. Results will have external validity, as the technique may be easily applied to maternity populations outside Australia. In summary, the results of this trial will contribute High level evidence on the impact of SWI on intrapartum CS rates and provide evidence of the analgesic effect of SWI on back pain.

## Background

Caesarean sections (CS) have risen annually in Australia for over 10 years reaching 31.6% of births in 2010
[1] (Figure 
1), compared with the Organization for Economic Co-operation and Development average of 26% in 2009
[2]. A previous CS increases the likelihood of a repeat caesarean section; and is associated with major obstetric complications in subsequent births
[3,4]; reduced fertility
[5-8], and increased risk of ectopic pregnancy and spontaneous miscarriage
[9]. Caesarean section has been associated with an increased likelihood of admission to neonatal intensive care nurseries
[10-12] and an increased risk of neonatal mortality
[13], and stillbirth in subsequent pregnancies
[14,15].

**Figure 1 F1:**
[figure not shown]
**Caesarean section and instrumental births, 2001 to 2010 **[1]**.**

The increasing CS rate imposes significant costs on health care systems with current Australian estimates placing the average cost for vaginal birth between $A3626-$A8907 compared with CS at $A8022-$A15229, depending on complications and insurance status
[15]. Interventions in labour also add to the costs. For example, a cost analysis on the use of epidural anaesthesia in labour demonstrated an increase in the cost of vaginal birth by 30% and CS by 150%
[16] (Figure 
2). This cost calculation did not include the increased length of inpatient stay related to these interventions or other co-morbidities and complications that may occur.

**Figure 2 F2:**
[figure not shown]
**Increase in costs as rates of intervention increase for low risk primiparous women in Australia (adapted with permission from **[16]**).**

### Lower back pain in labour – a significant problem

One in three women will experience continuous lower back pain in labour
[17]. The occipito-posterior (OP) position of the fetus has been cited as a common contributing factor
[18] although there is a paucity of evidence to support or refute this observation
[19]. The OP position results in deflexion of the fetal head, which then presents a larger diameter as it enters and progresses through the maternal pelvis, hence contributing to obstructed labour and an increased risk of interventions including epidural anaesthesia and caesarean section
[20]. Labour dystocia, characterised by very slow progress in labour together with significant and prolonged pain, further increases the risk of intervention, particularly epidural anaesthetic and CS
[20]. Indeed, labour dystocia has been reported as the major reason for a CS during labour
[21]. However, due to differences in Australian state and territory perinatal reporting, no data are available on the actual number performed for this reason. That said, a major Australian metropolitan hospital reported labour dystocia as the primary indication for 12.4% of all CSs performed in 2007
[22], with other research suggesting it was more common in women having their first baby (primiparous), accounting for nearly 80% of CSs performed during labour
[23].

### Problems related to epidural for lower back pain in labour

Although epidural anaesthesia remains the most effective form of analgesia available to women in labour, substantial evidence describes a strong association between epidural use and persistent OP position and subsequent labour dystocia
[20,24,25]. Epidural anaesthesia relaxes the pelvic floor muscles, disrupting the normal mechanisms of flexion and rotation of the fetal head that would otherwise facilitate a fetus in a malposition (OP) to self-correct
[20,24,25]. There is some evidence to suggest that epidural use may be associated with an increase in instrumental birth and CS, particularly in nulliparous women
[26]. Furthermore, epidural anaesthesia during labour is associated with co-morbidities arising from the need for urinary catheterisation to prevent urinary retention
[27]. Urinary catheterisation is a primary source of urinary tract infection (UTI) with one study reporting an incidence of 30% amongst women who were catheterised during labour
[28]; postpartum urinary retention and incontinence as a consequence of labour-related epidural use has also been reported
[29-32].

### Sterile water injections as pain relief for lower back pain in labour

Sterile water injections (SWI) into the lower back can provide pain relief to women experiencing lower back pain during labour although there is still uncertainty about the effectiveness of this intervention on the improvement of clinical outcomes including decreased need for epidural anaesthesia or CS
[33]. A sterile water injection, administered either intradermally or subcutaneously, causes osmotic and mechanical irritation resulting in a brief (15–30 second) but significant stinging sensation that is generally well tolerated by women. The onset of pain relief follows almost immediately in the majority of women and can last for up to two hours. The procedure can be repeated a number of times
[34]. The method has been described as inexpensive to use and the injection technique is easy to learn
[35].

### Review of previous trials of SWI in labour and effect on CS rates

A systematic review and meta-analysis
[36] undertaken on SWI reported significant limitations. The meta-analysis included eight trials involving 828 women and found a CS rate of 4.6% in the sterile water injection groups and 9.9% in the control groups (RR 0.51, 95% CI: 0.30-0.87)
[36]. Women in the control groups received normal saline placebo (six trials), acupuncture (one trial) and standard care defined as massage, water immersion and unrestricted mobilisation or transcutaneous electronic nerve stimulation (one trial). The authors reviewed the original publications of trial results and identified the following limitations:

•Only two reported a sample size calculation *a priori*[37,38]

•The method of allocation concealment was not described in two trials
[39,40]

•It was unclear if the outcome assessment was blinded in two trials
[39,41]

•Only one trial reported complete data on pain scores as many women gave birth prior to the final data collection point
[37]

•Two trials did not report if additional modes of pain relief had been used following the SWI intervention
[37,38]

•Only one of the investigators reported rates of cephalopelvic disproportion between groups
[41].

The trials were all relatively small, were heterogeneous using different techniques for administering SWIs and assessing outcome measures, and contained a number of potential biases. With these limitations, it is impossible to attribute any relationship between lower CS rates in the sterile water group to the administration of SWI. Further, none of these trials had investigated the relationship between SWI and CS as the primary outcome; to our knowledge, no such study has been undertaken. The authors of the meta-analysis, noting the reduction in CS rates and the limitations in the current literature, recommended a large trial with CS as the primary outcome. The National Institute of Clinical Excellence (NICE) guidelines
[33] also call for research into the effect of SWI on birth outcomes. With these issues in mind, we have designed the trial outlined in this protocol following the Consolidated Standards of Reporting Trials (CONSORT) guidelines
[42].

### Gaps in the research on SWI as pain relief in labour

This will be the first clinical trial statistically powered to identify if the addition of SWI to standard maternity care is superior to standard care alone with CS rates as the primary outcome. Furthermore, there is limited information about analgesia, epidural anaesthesia use and birth outcomes following sterile water injections in labour. For example, it is not clear whether rates of instrumental vaginal deliveries are affected by the intervention. Combined results from the two trials
[40,41] measuring this outcome show a trend towards an increased instrumental birth rate in the SWI group (OR 1.91; 95% CI 0.95-3.84). Finally, none of the trials have included a cost benefit analysis; we intend to undertake such an analysis.

## Methods/design

### Null hypothesis

H_0_: There will be no difference in the CS rate in women experiencing lower back pain in labour when comparing those who receive SWI with those who receive placebo.

H_1:_ There will be at least a 30 per cent relative difference in CS rates between the treatment groups.

### Aims

#### Primary aim

To determine if sterile water injections, as an intervention for back pain in labour, will reduce the in labour CS rate.

#### Secondary aims

To determine the effects of SWI for back pain in labour on:

•effectiveness for relieving back pain

•requirement for pain relief methods other than the intervention

•mode of birth and complications associated with birth (prior to hospital discharge)

•other maternal and infant outcomes in the immediate (six weeks) postnatal period

•cost of care for women and their babies during labour and birth, and the inpatient postnatal period from the perspective of the health system.

### Study design

A randomised, placebo controlled, double blind trial where participants receive either SWI or injections of a normal saline placebo. This trial will be conducted across maternity centres in Australia. The study protocol is registered on the Australian New Zealand Clinical Trials Registry (No ACTRN12611000221954). Six hospitals have confirmed involvement.

### Participants

Women in labour with lower back pain who satisfy the inclusion and exclusion criteria will be recruited from Australian maternity centres.

#### Inclusion criteria

Women who:

•In labour (spontaneous or induced, but not dependent on degree of cervical dilation)

•Are ≥ (equal to or greater than) 18 years of age

•Have a term singleton pregnancy (between 37 + 0 and 41 + 6 weeks gestation)

•Have a fetus in a cephalic (head down) presentation

•Experience back pain assessed by visual analogue scale VAS as ≥ 7 when women request analgesia for back pain

•Are able to provide informed consent.

#### Exclusion criteria

Women will be excluded if they fulfil any of the following criteria

•Multiple pregnancy

•Malpresentation (breech, transverse, shoulder)

•Previous CS

•Infection or inflammation at the injection sites or complications that could cause bleeding at injection site eg. Thrombocytopenia.

•Private insurance status

Private insurance status refers to women who utilise their health insurance to enable intrapartum care to be provided by the obstetrician of their choice. Only one site routinely offers women this model of care, whilst all sites offer obstetric care provided by publically a funded health system. Furthermore the use of private health insurance for obstetric care has also been associated with higher rates of CS than for those women receiving obstetric care through the public health system
[43,44].

### Recruitment and consent process

This trial requires the recruitment and consent of women in labour. Pain associated with labour, together with the possible use of pharmaceutical analgesic agents including narcotics, may impact on a woman’s capacity to understand new information and make informed decisions, including whether to participate in research. By way of acknowledging the Australian National Statement on Ethical Conduct in Human Research
[45] which recognises pregnant women as a potentially vulnerable group, consent processes in this study will reflect National Health and Medical Research Council (NHMRC) guidelines 4.1.1 to 4.1.10
[45]. That said, recent evidence suggests that women in labour are able to consent to participation in research, particularly when a staged approach is used
[46]. This may be achieved by providing information well in advance of recruitment, for example during the antenatal period, which allows prospective participants time to consider it and discuss their potential involvement in the research with family members and significant others, including health care providers
[46,47].

Recruitment will be undertaken at five metropolitan and regional maternity units in Queensland (QLD) and one metropolitan unit in New South Wales (NSW)). Hospital-based antenatal care providers will offer all eligible women a participant information and consent form (PICF) and discuss the purpose and design of the study during the antenatal period. As most participating hospitals, require women to return to the antenatal clinic in the third trimester of pregnancy (between 32 and 36 weeks), this provides an ideal opportunity to disseminate information, briefly discuss the study, and answer any immediate queries arising. At sites that do not employ this method of contact, the PICF will be provided at the time of booking into the hospital and distributed through the antenatal education classes. Consent will not be sought in the antenatal period. Contact details for the trial co-ordinators at each site are included on the PICF to enable women to seek more information if desired.

When women are in labour, they typically present to the Birth Suite of their respective hospital. Women will not be asked to consent to participation until such time as they have been fully assessed for eligibility against the inclusion and exclusion criteria. Although the majority of women will have received information regarding the trial during pregnancy, on admission to Birth Suite, staff will remind them of the trial and offer interested, and potentially eligible, women another copy of the PICF, and answer any outstanding questions.

Consent processes will be undertaken by the clinical trial co-ordinator at each site, or in their absence, a midwife who is not providing direct care to the woman. In our previous trial
[48], women had no objections to consenting in labour, and when they were requesting analgesia for back pain. However as consent for clinical care differs from that required for research, if the person seeking consent considers that labour is too far advanced, or for any other reason staff consider women to be incapable of considering all available choices in clinical care, and of making an informed and voluntary consent, participation in the trial will not be sought.

Once the consent process has been completed, the woman will be randomised.

### Sample size

The meta-analysis of SWI use reported the overall rate of ‘in labour’ CS as 9.9% in the control group and 4.6% in the intervention (SWI) group
[36] – i.e. a greater than 50% reduction in the CS rate in the SWI group. However, the review included trials where women receiving SWI were compared with women receiving either a placebo or other interventions (eg. acupuncture), and included trials that were conducted over two decades ago (1990 to 2008): a significant increase in CS rates (% in 1991
[49] to 31.5% in 2009
[50]) has been recorded in the intervening period.

More recently, at a metropolitan hospital in QLD, routine birth outcome data were collected on all women in labour who received SWI during 2010 (n = 427). The CS rate for women in the SWI group was 12.5%. The ‘in labour’ CS rate for women receiving standard care during the same period was 17.5%. This represents a difference of 30% which we suggest may conservatively reflect the contemporary clinical trend in CS rates. To demonstrate a similar reduction (17.5% to 12.5%), our study requires 839 women in each group (80% power, type I error 0.05). The attrition rate in our previous trial was 13%
[48], however this was largely due to women giving birth prior to the measurement of the primary outcome (pain at 30 mins) and the use of nitrous oxide inhalation prior to randomisation. Neither of these are exclusion factors in this trial, therefore we expect attrition to be minimal and propose an attrition rate of 10%. The total sample size required is therefore 1886 women. As some sites have higher annual birth rates than other sites, the recruitment allocation anticipated for each site will be proportional.

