## Data analysis

### Statistical methods

All women who underwent randomisation will be analysed in their allocated treatment groups (ie. intention to treat). Relative risks with 95% confidence intervals for the primary outcome will be calculated. Secondary outcome measures of categorical data will be analysed with chi-squared tests and continuous data will be analysed with t-tests for normally distributed data and Mann–Whitney *U* test for parametric data. Regression will be used if necessary to adjust for any other confounding variables. All study outcomes will be analysed using a two-sided P value of < 0.05 to indicate statistical significance. The study is only powered to report the primary outcome and for secondary outcomes confidence intervals (CI) will be included as a measure of the effect size. Differences in pre and post VAS scores will be reported in the format recommended by the recent Cochrane Review
[54].

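### The enrolment target is 1866 in the abstract and 1886 in the sample size section; only 1866 follows from the stated inputs

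*Protocol article*

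**What the plan says.** The abstract of the protocol article, under Methods/design (Participants), gives the trial size as "1866 women in labour".

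The Sample size section derives the target. It takes a caesarean rate of 17.5% under standard care and 12.5% with sterile water injections, and states that "our study requires 839 women in each group (80% power, type I error 0.05". It mentions that 13% were lost in the group's previous trial, explains why most of that loss should not recur, and adopts 10% instead. It then concludes: "The total sample size required is therefore 1886 women".

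The Statistical methods section fixes the sidedness of the test: "All study outcomes will be analysed using a two-sided P value of < 0.05 to indicate statistical significance".

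The Data safety and monitoring section places the interim analysis at the point where half of the women have been enrolled. No part of the article explains why the two totals differ.

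**The concern.** Two current parts of the same document give different targets for the same trial, and the larger one is presented as the result of a calculation whose inputs are all printed. If that calculation gives the other number, the section that defines the target is wrong as written.

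What hangs on the number is practical. It says when recruitment is complete. The interim is defined as a fraction of it, so it falls at 933 or 943 women. The Sample size section also apportions expected recruitment among the sites, which presupposes one total. Anyone comparing achieved with planned enrolment needs a single figure: a trial that closes at 1866 has met its target by the abstract and is 20 short by the methods.

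**Working it through.** **Inputs**

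| Input | Value | Where |
|---|---|---|
| Caesarean rate, standard care (p1) | 17.5% | Sample size |
| Caesarean rate, sterile water (p2) | 12.5% | Sample size |
| Power, type I error | 80%, 0.05 | Sample size |
| Sidedness | two-sided | Statistical methods |
| Evaluable women per group | 839 (1678 in all) | Sample size |
| Attrition adopted | 10% | Sample size |
| Total | 1886 | Sample size |
| Total | 1866 | Abstract |

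**Step 1. Reproduce the 839.** With d = p1 − p2 = 0.05 and mean rate p = 0.15:

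- n = [1.960·√(2·0.15·0.85) + 0.8416·√(0.175·0.825 + 0.125·0.875)]² / 0.05²
- n = (0.9897 + 0.4240)² / 0.0025 = 799.4 per group, rounded up to 800
- With the continuity correction: n′ = (n/4)·[1 + √(1 + 4/(n·d))]² = (799.4/4)·(1 + 1.0488)² = 838.9, rounded up to **839**

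This matches the protocol exactly, so the starting point of the last step is not in doubt. The other formulas tried do not give 839: unpooled variance 797, arcsine 796, one-sided 630 (669 with the correction).

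**Step 2. Allow for attrition.**

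| Rule | Calculation | Total |
|---|---|---|
| Divide by 0.9, per group | 839/0.9 = 932.2, up to 933; × 2 | **1866** |
| Divide by 0.9, on the total | 1678/0.9 = 1864.4 | 1865 (1866 for equal groups) |
| Multiply by 1.1, per group | 839 × 1.1 = 922.9, up to 923; × 2 | 1846 |
| Multiply by 1.1, on the total | 1678 × 1.1 = 1845.8 | 1846 |

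None gives 1886. The first gives the abstract's figure.

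**Step 3. What would give 1886?** The implied loss is 1 − 1678/1886 = 11.0%, and the implied multiplier is 1886/1678 = 1.124. The per-group rule at 11% does reach it: 839/0.89 = 942.7, rounded up to 943, × 2 = 1886. The 13% from the previous trial does not: 839/0.87 = 964.4, up to 965, × 2 = 1930; or 839 × 1.13 = 948.1, up to 949, × 2 = 1898.

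**Step 4. Size of the difference.**

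| | Target 1866 | Target 1886 |
|---|---|---|
| Evaluable per group at 10% loss | 1866 × 0.9/2 = 839.7 | 1886 × 0.9/2 = 848.7 |
| Power without continuity correction | 81.9% | 82.3% |
| Interim at half enrolled | 933 | 943 |

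Power here is Φ{[d·√m − 0.9897] / √(0.175·0.825 + 0.125·0.875)}, where m is the evaluable number per group. The totals differ by 20 women, or 20/1886 = 1.06%.

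**The case against.** The strongest reply is that nothing of substance depends on this. Both totals keep at least 839 evaluable women per group at the assumed loss, so the stated power is met either way. The figure in the section that governs the design is the larger one, so following it cannot underpower the trial. Ten women more or fewer at the interim is immaterial, and the hypothesis, endpoint and test are untouched. All of this stands as a statement of size. It does not make the derivation right or tell the reader which total is the target.

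A second reply is that 1886 need not be a mistyped digit. At 11% attrition the per-group rule gives it exactly, so it may be left over from a different assumption, with the error in the printed rate rather than in the total. That cannot be ruled out from the document, and the digit-error explanation is only an inference. But this route contradicts both the printed 10% and the abstract, whereas 1866 agrees with both. It is a reason to ask the sponsor to confirm the rate, not a reason to leave the number alone.

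A third is that a gap of about 1% lies within the tolerance usually allowed when a sample size is re-derived. That tolerance is for formulas the reader has to guess. Here the number before inflation and the attrition rate are both printed, and what remains is one division.

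**Conclusion.** The concern holds. The two totals contradict each other, and 1886 does not follow from 839 per group with 10% attrition; 1866 does. The conclusion rests on the printed 839 (which reproduces), the printed 10%, and the usual rule of dividing by the retained fraction and rounding up within each group. The alternative rules in the working change the answer to 1865 or 1846, never to 1886.

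The consequence is small: 20 women, ten women's difference in the timing of the interim, and about 0.4 percentage points of power. This is an error in a core design figure, not an underpowered design. It should be corrected because the target and the interim are both read from it.

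**What to change.** In the Sample size section, change 1886 to 1866 and show the step: 839/0.9 = 932.2, rounded up to 933 per group, 1866 in total. State in the Data safety and monitoring section that the interim falls when 933 women have been enrolled.

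Before doing so, the sponsor should confirm that 10% is the intended attrition rate. If 11% was meant, the printed rate and the abstract have to change instead, and the interim falls at 943.

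The cost is one corrected number and a line of explanation. The design does not change.
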